## Abstract

**Background:**

More than half of the unaccompanied young refugees (UYRs) resettled in Europe report elevated levels of posttraumatic stress symptoms (PTSS) and comorbid symptoms. Earlier studies have highlighted the effectiveness of the trauma-focused preventive group intervention “Mein Weg” (English “My Way”), and the feasibility of trauma-focused cognitive behavioral therapy (TF-CBT) for UYRs. Both interventions are deemed to be empirically supported treatments (ESTs). However, UYRs seldom receive ESTs or, in fact, any treatment at all. In view of the high need and the limited treatment resources available, a stepped-care approach is indicated but has not been evaluated so far. The purpose of this trial is to compare the stepped-care approach BETTER CARE with usual care enhanced with screening and indication (usual care+).

**Methods:**

In a cluster randomized controlled trial involving *N* = 540 UYRs living in up to *N* = 54 child and youth welfare service (CYWS) facilities, BETTER CARE will be compared with usual care+. We will randomize clusters comprising a CYWS facility with at least one eligible psychotherapist. BETTER CARE consists of step (1) screening and indication and either step (2) preventive trauma-focused group intervention “Mein Weg” delivered by trained CYWS staff or step (3) TF-CBT delivered by trained community therapists and supported by trained translators if necessary. Participants will be assessed 6 and 12 months after randomization. The primary outcome is the severity of PTSS after 12 months. Secondary outcomes are depressive and anxiety symptoms, quality of life, and proxy reported PTSS. Furthermore, drug use, health costs, benefits, and long-term effects on integration/acculturation will be assessed.

**Discussion:**

The trial will directly integrate a stepped-care approach into existing structures of the German child welfare and (mental) health system. It could, therefore, serve as a blueprint for how to implement ESTs for UYRs. If successful, screening, prevention, and intervention will be sustainably implemented in CYWS in southern Germany.

**Trial registration:**

German Clinical Trials Register DRKS00017453. Registered on 11 December 2019.

**Supplementary information:**

The online version contains supplementary material available at 10.1186/s13063-020-04922-x.

## Background

Refugee minors often arrive in European host countries without their parents or other caregivers. In Germany, unaccompanied refugee minors have the possibility to remain in the care of child and youth welfare services (CYWS) up to the age of 21. We, therefore, use the terms minors and young adults when referring to unaccompanied young refugees (UYRs). However, there are reports that CYWS staff have been confronted with major challenges, for instance, limited professional experience and insufficient training [1]. A recent cross-sectional study showed that UYRs in southern Germany had experienced a high number of traumatic events, and presented elevated levels of posttraumatic stress symptoms (PTSS), depression, and anxiety [2]. Symptoms, especially within the re-experiencing cluster, seem to be central in this population [3], and they differ in this respect from other traumatized children and adolescent samples [4]. These findings are in line with several studies from other European countries reporting high PTSS rates from 20% [5] to 76% [6]. On average, symptoms tend to be stable over time [7] even though another recent study by Müller et al. [8] indicated a significant reduction in PTSS severity after 12 months. However, the rates for clinically relevant PTSS (38%) were still high. Additionally, UYRs often suffer from ongoing stressors in their host countries, so-called post-migration stressors, such as worries about their families or acculturation distress [9].

School- and community-based interventions in a group setting are one way of meeting the high demand for mental health care in vulnerable populations [10]. They offer low-threshold support even for individuals with sub-clinical PTSS. The 6-session trauma-focused preventive intervention “Mein Weg” (English “My Way” [11]) enables social workers in CYWS facilities to support UYRs with PTSS and related difficulties. In their randomized controlled trial with *N* = 99 UYRs, Pfeiffer and colleagues [12] demonstrated the effectiveness and sustainability of the trauma-focused group program [13]. The intervention manual, which is based on trauma-focused cognitive behavioral therapy principles, was specifically developed for UYRs in collaboration with CYWS facilities, for instance, by using pictures instead of writing, thus making them more accessible to UYRs with limited German language or reading skills [11]. Despite a number of publications on “Mein Weg” studies [12–15], it has not been evaluated as a preventive component within a stepped-care approach.

For UYRs who meet the diagnostic criteria of posttraumatic stress disorder (PTSD), an evidence-based, individual trauma-focused treatment by a mental health care professional is indicated [16]. Trauma-focused cognitive behavioral therapy (TF-CBT) [17] is one of the treatments with the most empirical support in western and non-western cultures [18]. As it includes a caregiver in treatment, it is specifically suited to improving social support outside of therapy for UYRs living in CYWS facilities. Unterhitzenberger and colleagues [19] enhanced the cultural sensitivity of TF-CBT for UYRs and verified its feasibility in an uncontrolled trial. In fact, TF-CBT is the only individual treatment that has been evaluated with UYRs up to now. Evidence in the context of an RCT and a stepped-care approach is lacking. TF-CBT has proven its effectiveness in the German health care system within an RCT in eight outpatient clinics [20]. The dissemination and sustainable implementation of TF-CBT in German routine care are now necessary.

Based on the authors’ preliminary work on the mental health of minor refugees, the effectiveness of “Mein Weg,” and the feasibility of TF-CBT for UYRs, the intervention to be evaluated is a stepped-care approach consisting of three main components: screening, preventive group intervention, and individual treatment. We call this approach BETTER CARE (see Fig. 1). Cascade, tier, or stepped-care models to treat traumatized refugees have been suggested before [21, 22] but have rarely been evaluated. Not only is there a lack of information on their effectiveness, but also on their implementation and health economic evaluation. The latter is especially relevant, as there are no data on the cost-effectiveness of PTSD treatments for UYRs in Germany and a stepped-care approach is supposed to be especially needs-oriented. BETTER CARE will be implemented in the routine care of CYWS and health services in Germany. Some studies have investigated general attitudes of CYWS staff towards the mental health treatment of their clients. Results show that CYWS staff perceive mental health treatment as necessary but rate cooperation between systems as difficult [23]. A systematic analysis of successful factors on the institutional level (e.g., motivation, capacity of facilities, collaboration with mental health sector) is necessary to ensure the implementation of BETTER CARE [24].

**Fig. 1 Fig1:**
[figure not shown]
The stepped-care approach BETTER CARE. CATS-2 = Child and Adolescent Trauma Screen 2; TF-CBT = trauma-focused cognitive behavioral therapy

## Methods

### Aims

We aim to implement and evaluate a screen and stepped-care approach for UYRs by providing empirically supported treatments (ESTs) through dissemination and implementation. The objectives are as follows:
To compare BETTER CARE with a control group (usual care plus screening and indication, usual care+) with regard to PTSS (primary goal).To implement and evaluate the preventive trauma-focused group intervention ‘Mein Weg’ delivered by trained and supervised social workers for UYRs with subclinical PTSS in CYWS facilities.To implement and evaluate an evidence-based treatment (TF-CBT) in clinical practice and specific TF-CBT training for interpreters.To assess the costs of care for UYRs and the cost utility of the BETTER CARE model in comparison to usual care+.To assess the readiness in CYWS facilities to collaborate with mental health services and the role of context factors in long-term developmental trajectories.

### Trial design

The current study is a cluster randomized controlled hybrid implementation-effectiveness trial with two active conditions (BETTER CARE versus usual care+). An independent institution (Institute of Epidemiology and Medical Biometry, Ulm University) will perform the randomization of clusters (CYWS facility and one therapist for 10 UYRs), stratified by the number of UYRs in the respective CYWS facility (≤ 20 UYRs = small, > 20 UYRs = big facility). Randomization will be done as stratified block randomization with permuted block length using the randomization software ROM [25]. Clusters will be randomized in either BETTER CARE or usual care+ after agreement to participate in the study, after attendance by CYWS staff in the initial information workshop, and after screening (T0) of participants of the respective facility is completed. Selection bias will be avoided by the large number of clusters (*N* = 54). See Fig. 2 for participant flow through the study.

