### Sample size

The sample size calculation was based on a two-step procedure due to the hierarchical data structure. First, we calculated the sample size for an individual randomized study based on our previous data. We assumed a small effect size (ES) of *d* = 0.2 for “Mein Weg” as this intervention is implemented with a non-clinical sample and a medium ES of *d* = 0.5 for TF-CBT. The latter ES reflects the fact that our previous trial with *d* = 1.08 (CATS [19]) was uncontrolled, and treatment was provided in a university setting with highly experienced therapists. We plan to compare BETTER CARE with usual care+ and expect a small effect (*d* ≥ 0.30) in favor of BETTER CARE at 12 months (T2) on the CATS-2. A power analysis for a t-test with independent samples (α = 0.05, two-tailed, power 0.80) results in a minimum sample size of 2 × 176 participants (352 in total). The second step will factor in the cluster structure of the data with participants nested within CYWS facilities/therapists clusters. We assume that each CYWS facility will recruit on average *n* = 10 participants. The design effect is needed for the inflation of the group sample size: DE = 1 + (*m* − 1) × ICC with the fixed cluster size *m* and the intra-cluster correlation coefficient ICC. For the fixed cluster size, a value of *m* = 8 was set because of an estimated dropout rate of 20% of participants (UYRs). For the ICC, a liberal value of 0.05 was assumed to control for the correlation of the outcome of participants living in the same facility. In this context, the DE is 1 + (8–1) × 0.05 = 1.35 which results in a group size of 352 × 1.35 = 476 participants. As every facility recruits 10 participants on average, 48 facilities are needed for the whole trial. With an assumed dropout rate of 10% of facilities, an oversampling of 6 facilities is needed, resulting in 54 facilities (= 2 × 27 facilities). Thus, the overall participant sample within these facilities is estimated as 54 × 10 = 540 participants.

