#### BETTER CARE arm

The stepped-care approach BETTER CARE includes the first step as described above (screening and indication). The second step refers to subclinical cases (CATS-2 score < 25). They will be allocated to the preventive group intervention “Mein Weg.” Participants above the clinical cut-off (≥ 25) will be referred to TF-CBT (step 3). UYRs with a CATS-2 score ≥ 25 who refuse to participate in TF-CBT or who have to wait more than 3 months for TF-CBT treatment will be invited to participate in “Mein Weg” (see Fig. 1).

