### Statistical analysis

We will analyze the primary outcome (CATS-2 severity score) using hierarchical linear mixed (HLM) models to account for the nesting of cases within clusters. Mixed effect models, with fixed effects of group (BETTER CARE vs usual care+) and time (intake (T0) versus 6 months (T1) versus 12 months (T2)) as well as their interaction, will be conducted. Primary outcome analysis will be based on the ITT sample (*N* = 540 participants) as the mixed model approach will take missing data and different numbers of reassessments per participant/patient into account. A significance level of *α* = 0.05 will be used. We will also use exploratory mixed linear models to examine the impact of other variables (gender, age, nationality, asylum status) on our primary outcome. Separate (hierarchical) linear mixed models will be used to analyze the secondary outcomes.

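### Facilities are stratified on size alone although their T0 CATS-2 is known before allocation; a T0 severity stratum and baseline adjustment would be a cheap gain in balance and precision

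*Protocol article*

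**What the plan says.** Protocol article, Trial design: "Randomization will be done as stratified block randomization with permuted block length". The only factor is size: allocation is "stratified by the number of UYRs in the respective CYWS facility", in two levels split at 20 UYRs. A facility is allocated "after screening (T0) of participants of the respective facility is completed". An independent biometry institute performs the randomisation. The section then states: "Selection bias will be avoided by the large number of clusters".

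Protocol article, BETTER CARE arm: participants with a T0 CATS-2 below 25 go to Mein Weg; those at 25 or above "will be referred to TF-CBT (step 3").

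Protocol article, Statistical analysis: the primary outcome, CATS-2 severity, is analysed in a mixed model "with fixed effects of group (BETTER CARE vs usual care+) and time", with T0, T1 and T2 as levels of time, plus the group-by-time interaction.

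**The concern.** When a facility is allocated, the T0 scores of all its participants on the primary outcome measure have been collected, and they are entered directly into the online tool (Data management and storage). The design does not use them. Balance on baseline severity is left to chance.

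Two things are at stake:

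- **The primary contrast.** The described model estimates the T0 group difference freely. The group-by-time contrast at T2 is then essentially a comparison of change from T0. A chance T0 difference enters such a contrast with the opposite sign, through regression to the mean. An arm that happens to start higher appears to improve more.
- **Case mix.** T0 severity decides which step is indicated, and Sample size assumes different effects for the two steps (d = 0.2 for Mein Weg, 0.5 for TF-CBT). The planned cost comparison (Aims) also depends on how many participants in each arm have an indication for therapy. Adjusting the primary model does not balance these.

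In addition, the sentence on selection bias gives the wrong reason. The number of clusters governs the size of chance imbalance. It does not protect against selection.

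**Working it through.** **The plan's own figure.** For d = 0.30, two-sided α = 0.05 and power 0.80, the t-test needs 175.4, so 176 per arm or 352 in total. 352 × 1.35 = 475.2, rounded up to 476; at 10 per facility, 48 facilities; 48 / 0.9 = 53.3, so 54. The plan's "resulting in 54 facilities (= 2 × 27 facilities") and "54 × 10 = 540 participants" are reproduced.

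**Inputs.** From Sample size: 54 facilities, 10 participants each at T0 (270 per arm), ICC 0.05, target 0.30 SD. The ICC is stated for the outcome; using it at T0 is an assumption. The T0–T2 correlation r is not given; 0.5 to 0.7 is assumed.

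**Chance difference at T0.**
- Design effect at T0, before dropout: 1 + (10 − 1) × 0.05 = 1.45
- SD of the arm difference: √(2 × 1.45 / 270) = 0.1036 SD
- 95% limit: 1.96 × 0.1036 = 0.203 SD, which is 68% of 0.30
- Expected absolute difference: 0.1036 × √(2/π) = 0.083 SD, which is 28% of 0.30
- About 34% of allocations exceed 0.10 SD and about 5% exceed 0.20 SD

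| ICC at T0 | 95% limit (SD) | Share of 0.30 |
|---|---|---|
| 0 | 0.169 | 56% |
| 0.02 | 0.183 | 61% |
| 0.05 | 0.203 | 68% |
| 0.10 | 0.233 | 78% |
| 0.15 | 0.259 | 86% |

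**Effect on the T2 contrast.** With T0 left free, the shift is −(1 − r) × imbalance. For 0.20 SD: 0.5 × 0.20 = 0.10 SD at r = 0.5, and 0.3 × 0.20 = 0.06 SD at r = 0.7.

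**Effect on indication.** If half the participants are at or above 25 and the same ICC applies (both assumed): 1.96 × √(2 × 0.25 × 1.45 / 270) = 0.102, about 10 percentage points either way.

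**What a T0 stratum would do.** Simulation of 6,000 trials: 54 facilities of size 8 + Poisson(2), ICC 0.05 at T0 and T2, r = 0.6, 30% large facilities, permuted blocks of 2, 4 and 6, T0 stratum split at the population mean.

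| | Size only | Size × T0 mean |
|---|---|---|
| SD of T0 difference | 0.103 | 0.067 |
| 95% limit of T0 difference | 0.202 | 0.129 |
| Trials above 0.15 SD | 14% | 2% |
| SD of change contrast | 0.0931 | 0.0872 |
| SD of baseline-adjusted contrast | 0.0839 | 0.0828 |

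A second simulation (20,000 trials, facilities of exactly 10, blocks of 4, mid-split T0 stratum without the size factor) gives a fall from 0.203 to 0.127 SD. At ICC 0.02 the limit falls from 0.184 to 0.113, and at 0.10 from 0.233 to 0.143.

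Variance of the change contrast: (0.0872 / 0.0931)² = 0.88, so about 12% less with the stratum. Baseline adjustment without the stratum: (0.0839 / 0.0931)² = 0.81, so about 19% less. Adding the stratum to an adjusted analysis: (0.0828 / 0.0839)² = 0.974, so a further 2.6%.

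**Dependence on the cut.** Facility means have SD √(1.45 / 10) = 0.38. For normal facility means and ignoring incomplete blocks, a cut 0.5 SD (participant scale) from the population mean puts about 10% of facilities in one stratum, and the 95% limit is about 0.166. At 0.75 SD it is about 0.189, close to the 0.203 without the stratum.

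**The case against.** The strongest reply is that nothing here is an error. Stratified blocks on cluster size are a valid design. Chance imbalance is already part of the standard error, so type I error and coverage hold. The model includes T0, and the exact contrast and any constraint on T0 may be set in an analysis plan that is not shown. With adjustment, the stratum adds only 2.6% in variance. Most of this stands. It limits the point to an improvement and makes baseline adjustment the main remedy for precision. It does not remove the case for the stratum: the stratification factors are fixed in the protocol, and no later analysis plan can balance case mix and indication once facilities are allocated.

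Stronger readings that a reader might infer are not supported:

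- **That 0.20 SD is a ceiling.** It is a 95% limit, exceeded in about 5% of allocations; the typical difference is under a third of the target.
- **That the number of clusters is the main cause.** With ICC 0, which corresponds to randomising 540 individuals, the limit is already 56% of the target.
- **That a T0 difference passes in full into the 12-month effect.** It does not under the described model. The shift of r × imbalance (0.10 to 0.14 SD) belongs to a T2-only comparison, which Statistical analysis does not describe.
- **That the trial is open to selection bias at allocation.** The sentence is wrong in its reasoning, but the same section already provides T0 before randomisation and independent allocation.

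**Conclusion.** The point holds as a low-cost improvement, not as a flaw that invalidates the trial. The design holds each facility's baseline on the primary measure at the moment of allocation and does not use it. At an assumed T0 ICC of 0.05, the 95% limit of the chance T0 difference is about 0.20 SD. In a change contrast with T0 free, an imbalance of that size moves the estimate by 0.06 to 0.10 SD, a fifth to a third of the target, for assumed r of 0.5 to 0.7. The share indicated for TF-CBT can differ by about 10 percentage points if about half are above the cut-off. Baseline adjustment recovers most of the lost precision; the stratum then serves mainly balance of severity and indication. The simulated gains rest on r = 0.6 and a split near the middle of facility means. The documents give no CATS-2 mean or SD for this population, so whether 25 lies near that middle cannot be judged from them.

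**What to change.** 1. In Trial design, add a second stratification factor for facilities not yet randomised: mean T0 self-report CATS-2, in two levels, with a cut fixed in advance near the expected middle of facility means. Use 25 only if facility means are expected to centre there. The Trial status section in the Discussion reports no facility randomised at submission.
2. In Statistical analysis, state how T0 enters the primary model: as a covariate, or as an outcome level with T0 means constrained equal across arms. Include the new stratification factor if it is adopted.
3. Replace the sentence on selection bias with the safeguards already described: T0 completed before randomisation, and allocation by an independent institution.

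Cost: a revised randomisation specification and a few protocol sentences; no new data, visits or participants. Each facility's T0 data must be scored before allocation. Four strata instead of two leave more incomplete blocks, so cluster counts per arm can differ somewhat more (simulated 95% limit 4 instead of 2 of 54).

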**Fig. 2 Fig2:**
[figure not shown]
Participant flow. AUDIT = Alcohol Use Disorder Identification Test; BAOS = Brief Acculturation Orientation Scale; BSAS = Brief Sociocultural Adaptation Scale; CATS-2 = Child and Adolescent Trauma Screen 2; CUDIT-R = Cannabis Use Disorder Identification Test, Revised; CYWS = Child and youth welfare service; DSSYR = Daily Stressors Scale for Young Refugees; GAD-7 = Generalized Anxiety Disorder 7; GCIC = Group Climate Instrument for Children; PHQ-9 = Patient Health Questionnaire 9; SSQ = Social Support Questionnaire; TF-CBT = trauma-focused cognitive behavioral therapy; UYR = unaccompanied young refugee; WHOQOL-BREF = World Health Organization Quality of Life, brief version

The study protocol was written in accordance with the SPIRIT 2013 statement (Standard Protocol Items: Recommendations for Interventional Trials; for the SPIRIT Checklist, see Additional file 1).

### Study setting and recruitment

As this is a dissemination and implementation trial, assessment and intervention will take place in a naturalistic setting: the CYWS facilities in which the UYRs live, private practices, and outpatient clinics. Researchers from university clinics will be involved in instructing screenings and implementing the interventions (workshops, case consultation). However, they will not be involved in providing group or individual treatments themselves.

Recruitment will last 24 months and will focus on CYWS facilities serving UYRs and not on UYRs themselves. We will use the following recruitment strategies: letters of invitation to the CYWS, half-day symposia for CYWS staff (presentation of previous findings, the study, and its components), provision of flyers for youth welfare offices and central authorities as well as non-statutory agencies. To recruit therapists, we will publish papers in widely distributed journals for German mental health professionals, and we will send out information by e-mail through professional organizations and personalized information letters. General additional recruitment efforts will include a study website, press interviews, distribution of flyers, and talks at mental health and/or refugee care events.

### Trial status

This study protocol is version 1 from July 4, 2019. Recruitment of CYWS facilities began on July 13, 2020, and is scheduled to be completed on January 1, 2022.

